## Abstract

**Background:**

Haemostasis in liver surgery remains a challenge despite improved resection techniques. Oozing from blood vessels too small to be ligated necessitate a treatment with haemostats in order to prevent complications attributed to bleeding. There is good evidence from randomised trials for the efficacy of fibrin sealants, on their own or in combination with a carrier material. A new haemostatic device is Sangustop^®^. It is a collagen based material without any coagulation factors. Pre-clinical data for Sangustop^® ^showed superior haemostatic effect. This present study aims to show that in the clinical situation Sangustop^® ^is not inferior to a carrier-bound fibrin sealant (Tachosil^®^) as a haemostatic treatment in hepatic resection.

**Methods/Design:**

This is a multi-centre, patient-blinded, intra-operatively randomised controlled trial. A total of 126 patients planned for an elective liver resection will be enrolled in eight surgical centres. The primary objective of this study is to show the non-inferiority of Sangustop^® ^versus a carrier-bound fibrin sealant (Tachosil^®^) in achieving haemostasis after hepatic resection. The surgical intervention is standardised with regard to devices and techniques used for resection and primary haemostasis. Patients will be followed-up for three months for complications and adverse events.

**Discussion:**

This randomised controlled trial (ESSCALIVER) aims to compare the new collagen haemostat Sangustop^® ^with a carrier-bound fibrin sealant which can be seen as a "gold standard" in hepatic and other visceral organ surgery. If non-inferiority is shown other criteria than the haemostatic efficacy (e.g. costs, adverse events rate) may be considered for the choice of the most appropriate treatment.

**Trial Registration:**

NCT00918619

## Background

All surgical procedures inevitably lead to bleeding. Haemostasis - the control of bleeding - aims at reducing the amount of blood loss and the need for transfusion as well as preventing re-bleeding, haematoma formation with subsequent morbidities, and the need for intervention or repeat surgery. During liver resection the control of bleeding is a major concern. The liver is predisposed to a diffuse bleeding because of its extreme vascularity, particularly because of the hepatic sinusoidal structure, which does not have smooth muscles capable of contraction to induce vasoconstriction.

Surgical techniques and devices to facilitate haemostasis have been developed in the last decades and have minimised operative risks of liver resection. Nevertheless, a parenchymal transsection of the liver tissue is always associated with some degree of bleeding due to the division of small blood vessels which can not be isolated and ligated.

In order to achieve control over that parenchymatic diffuse bleeding from the resection surface and to prevent intraperitoneal complications attributed to bleeding various locally applicable agents (haemostats) are in use. These haemostats include bone wax, gelatine, collagen, oxidized regenerated cellulose, fibrin sealant glues, and synthetic glues [1]. Some evidence from randomized controlled trials (RCT) exists regarding the use of fibrin sealants on their own or combined with a collagen fleece [2,3].

A composite product with well documented efficacy is Tachosil^® ^[Nycomed, Linz, Austria]. It consists of a collagen fleece carrying the fibrin glue components human fibrinogen and human thrombin. It was shown in a RCT to be superior in obtaining intraoperative haemostasis over argon beamer in liver resection [4]. The time to haemostasis was significantly reduced. Also in kidney tumour resection a randomized study showed superiority over standard suturing [5].

A new haemostat product is Sangustop^® ^[Aesculap, Tuttlingen, Germany]. It is indicated for local haemostasis of capillary bleeding and bleeding of parenchymal organs. Sangustop^® ^is composed of native absorbable collagen fibrils without any blood serum products or any pharmaceutical activity. The felt structure being rich in surface gives a framework for the adhesion of blood platelets, thus provides an additional impetus to clotting. Pre-clinical data showed very good haemostatic activity, superior to sealant and to cellulose product [6].

The aim of this study is to show that the new microfibrillar collagen hemostat Sangustop^® ^is not inferior to the carrier-bound fibrin sealant Tachosil^® ^with regards to haemostatic efficacy. The efficacy of Tachosil^® ^has been shown in many clinical studies in various indications and thus can be seen as a standard treatment superior to other locally applicable agents [4,5].

## Methods/Design

### Objectives

This study is designed as a prospective, single blinded, randomized, 2-arm trial of two haemostatic products. The primary objective of the study is to show the non-inferiority of Sangustop^® ^(Treatment Arm 1) versus Tachosil^® ^(Treatment Arm 2) in achieving haemostasis after hepatic resection.

#### Primary endpoint

▪ Haemostasis 3 minutes after application of the haemostatic product.

#### Secondary endpoints

▪ Haemostasis 5 minutes after application of the haemostat product.

▪ Haemostasis 10 minutes after application of the haemostat product.

▪ Time to haemostasis

▪ Complications and adverse events intra-operatively during liver resection and during 3 months of follow-up.

### Interventions

#### Surgery

Liver resection (segmental or non-segmental) will be performed according to accepted surgical standards. Surgeons must be board certified and must have a minimum experience of 10 liver resections performed. A standardization of surgical technique will be done inasmuch as there is a restriction in the methods allowed for resection and for primary haemostasis.

The following techniques of liver resection are allowed:

▪ Cavitron Ultrasonic Aspiration (CUSA^®^)

▪ Hydrojet (pressurized jet of water)

▪ Clamp Crushing

▪ Scissors

▪ Stapler transsection

The following techniques of liver resection are not permitted:

▪ Argon beamer (Argon-Plasma Coagulation)

▪ Radiofrequency-assisted devices for parenchymal division (e.g. Habib™-Sealer, TissueLink™)

▪ Ultrasonic dissection (e.g. UltraCision^®^)

The following methods of primary haemostasis are allowed:

▪ Vascular clips

▪ Sutures

All other methods of primary haemostasis (e.g. Argon Laser, bipolar coagulation) are not permitted.

After primary haemostasis has been achieved and with persistent parenchymal bleeding the patient will be randomized to one of two treatment groups. Either Sangustop^® ^or Tachosil^® ^will be applied to the resection area according to the respective instructions for use and the time to haemostasis will be recorded.

#### Follow-up

After surgery, two follow-up examinations will be performed while the patients are still hospitalised. Patients are observed for 3 months for documentation of adverse events. See Table 1 for detailed follow-up.

**Table 1 T1:** Flow-Chart: Overview Clinical Trial Study Activities

Visit	1 Screening	2 Surgery	3 Follow-up 24 hrs after surgery	4 Follow-up 7 days after surgery	5 Follow-up 30 after surgery	6 Follow-up 3 months after surgery
Informed consent	x					

Demographics	x					

Medical history	x					

Medication history	x					

Physical examination	x					

Blood and urine examinations	X**^1, 4^**	X**^1^**	X**^1^**			

Eligibility Criteria	X**^2^**	X**^3^**				

Randomisation		X				

Liver resection (Resection area, weight, histopathology, prim. haemostasis)		X				

Investigational treatment		Sangustop^®^/Tachosil^®^				

Number of Sangustop^® ^Compresses/Tachosil^® ^Sponges used		X				

Time to haemostasis		X				

Required blood transfusions				X		

Central venous pressure		X				

Adverse events incl. complications		X	X	X	X	X

^1^Blood: INR, PTT, Hb, Ht; ^2^1st part; ^3^2nd part, ^4^Blood or urine: pregnancy test.

#### Study materials

Sangustop^® ^(B. Braun Aesculap, Tuttlingen, Germany) is a felt-like haemostatic agent, composed of native absorbable collagen fibrils of bovine origin and containing riboflavin as a colouring agent.

TachoSil^® ^(Nycomed, Linz, Austria) is a ready-to-use fixed combination of a patch sponge (equine collagen) coated with a dry layer of the human coagulation factors fibrinogen and thrombin.

Both investigational products of this clinical trial are approved for clinical use (CE-mark and EU Marketing Authorisation, respectively). They will be used according to respective instructions for use within their usual range of indication.

### Trial population

Clinical trial participants will be recruited in the clinical trial centres consecutively from a population of patients who are planned for an elective liver resection. A detailed overview of the eligibility criteria is given in Table 2. One part of the eligibility criteria are checked preoperatively. A second set of criteria must be checked intra operatively. Patients who do not meet the second part of the eligibility criteria will neither be randomised nor treated with an investigational product. Their trial participation will end by this time. Regular monitoring visits will be performed and the eligibility of all enrolled patients will be checked by source data verification. Resection area will be calculated with the aid of a paper blot of the resection surface.

**Table 2 T2:** Eligibility Criteria

Inclusion Criteria	Exclusion Criteria
▪ Age: >18 years ▪ Patients with an indication for liver resection (segmental or non-segmental) ▪ Willing and able to complete the clinical trial procedures, as described in the protocol ▪ Signed written informed consent to participate in this clinical trial	***Criteria to be checked at screening visit:*** ▪ Presence or sequelae of coagulation disorder, liver cirrhosis, Klatskin tumour ▪ Concurrent participation in another clinical trial with a medical device or medicinal product or with interfering endpoints ▪ Concurrent or previous therapy with systemic pharmacologic agents promoting blood clotting including but not limited to tranexamix acid, activated factor VII, and aprotinine ▪ Known allergy or hypersensitivity to a component of the investigational treatments Sangustop^® ^or Tachosil^®^, to riboflavin or to proteins of bovine origin ▪ Pregnancy or breast feeding ▪ Inability to understand the nature and the extent of the trial and the procedures required
	***Criteria to be checked during surgery:*** ▪ Resection area estimated by operating surgeon <16 cm^2^ ▪ Infected wound area ▪ Persistent major bleeding after primary haemostasis ▪ No bleeding after resection

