### Sample size

The sample size was calculated to test for non-inferiority of Treatment Arm 1 (Sangustop^®^) versus Treatment Arm 2 (Tachosil^®^) in terms of haemostasis 3 minutes after application of the haemostatic product. The proportion of patients with a complete haemostasis 3 minutes after application will be assessed. In a previous study [4] the proportion of patients with complete blood clotting after 3 minutes for Tachosil^® ^was estimated to be 73%.

With 60 subjects in each group, the lower limit of the observed one-sided 97,5% confidence interval will be expected to exceed -0,100 with 93% power when the proportion of Treatment Arm 2, π_S_, is 0,730 and the expected proportion of Treatment Arm 1, π_T_, is 0,880; results are based on 100 simulations using the Newcombe-Wilson score method to construct the confidence interval [7].

In case of non-inferiority an additional two group χ^2^-test with a 0,050 two-sided significance level will have 83% power to detect the difference between an Treatment Arm 2 proportion, π_1_, of 0,730 and an Treatment Arm 1 proportion, π_2_, of 0,930 (odds ratio of 4,914) when the sample size in each group is 60.

Assuming a drop-out rate of 5% a total number of 126 patients needs to be enrolled. Figure 1 shows a flow diagram of the progress through the trial phases.

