### Statistical analysis

#### Primary Variable

The proportion of patients with haemostasis 3 minutes after application of the haemostat product as well as associated 95% confidence intervals will be reported for each treatment arm. The study null hypothesis is that Tachosil^® ^is more effective than Sangustop^®^. Non-inferiority will be demonstrated if the lower limit of the observed two-sided 95% confidence interval of the observed difference in proportions of Treatment Arm 1 - Treatment Arm 2 does not fall below -0.100. The analysis will be based on the per-protocol population and repeated for the intent-to-treat population. The intent-to-treat population consists of all consenting patients randomized into the study. The safety population comprises all treated patients. The Per-Protocol population excludes all patients who violated inclusion or exclusion criteria of the protocol.

If the 95% confidence interval for the treatment effect not only lies entirely above -0.1 but also above zero then there is evidence of superiority in terms of statistical significance at the 5% level. The difference in proportions between the two treatment arms (Treatment Arm 1 versus Treatment Arm 2) will be tested with a Fisher's exact test to reject the null hypothesis of no difference.

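### The unadjusted primary difference is valid, but it leaves resection area unused, although the cut surface is fixed before allocation and area is recorded, so a modest gain in precision may be lost

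*Protocol article*

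**What the plan says.** Under Primary Variable, non-inferiority is shown if the lower 95% limit of the "observed difference in proportions of Treatment Arm 1 - Treatment Arm 2 does not fall below -0.100". For superiority, the two proportions "will be tested with a Fisher's exact test to reject the null hypothesis of no difference". Neither step uses a covariate or a stratum. Under Randomisation and blinding, allocation is stratified by centre only.

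Resection area appears in three places:
- The flow-chart under Follow-up schedules it at the surgery visit: "Liver resection (Resection area, weight, histopathology, prim. haemostasis".
- Trial population says how it is obtained: "Resection area will be calculated with the aid of a paper blot of the resection surface".
- Table 2 excludes patients whose area the surgeon puts below 16 cm², a check made during surgery.

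Under Surgery, randomisation follows resection and primary haemostasis. Under Randomisation and blinding, it takes place just before the product is applied.

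**The concern.** The endpoint is haemostasis of an oozing cut surface, so the size of that surface may well predict it. With about 60 patients per arm and no stratification by area, one arm can by chance receive larger surfaces, and the crude difference then moves with that imbalance. Adjusting for a prognostic value fixed before allocation removes that part of the random variation and narrows the interval. Precision matters here because the planned power rests on Sangustop being 15 points better than Tachosil. If both true rates are 0.73, the crude analysis has only about 24% power to show non-inferiority.

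**Working it through.** **Inputs from Sample size and Primary Variable.** 60 per arm; rates 0.88 (Sangustop) and 0.73 (Tachosil); margin -0.10; one-sided 2.5% level. The document gives no link between area and haemostasis, so its strength is assumed below.

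**1. The plan's own figure.** It states that "the lower limit of the observed one-sided 97,5% confidence interval will be expected to exceed -0,100 with 93% power".
- Exact binomial enumeration of the Newcombe-Wilson lower limit gives 94.1%.
- Normal approximation: SE = √[(0.88×0.12 + 0.73×0.27)/60] = √(0.3027/60) = 0.0710. Power = Φ(0.25/0.0710 − 1.96) = 94.1%.
- The stated 93% comes from 100 simulations, with Monte Carlo error √(0.93×0.07/100) = 2.6 points. It reproduces.

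The sample size therefore matches the crude analysis.

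**2. Effect of adjustment, by formula.** If area explains a share R² of the outcome variance, the SE becomes SE×√(1 − R²).

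| Assumed R² | SE | 95% half-width | Power at 0.88 v 0.73 |
|---|---|---|---|
| 0 | 0.0710 | 0.139 | 94.1% |
| 5% | 0.0692 | 0.136 | 95.1% |
| 10% | 0.0674 | 0.132 | 96.0% |
| 20% | 0.0635 | 0.125 | 97.6% |

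**3. Effect of adjustment, by simulation.** 4,000 trials per setting, 60 per arm, one standard-normal covariate (log area in SD units), logistic outcome set to the stated marginal rates. The crude difference with a Wald interval is compared with a standardised risk difference and influence-function interval. At 0.88 v 0.73:

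| Assumed odds ratio per SD | SE crude → adjusted | Power crude → adjusted |
|---|---|---|
| 1.0 | 0.0714 → 0.0717 | 94.0% → 93.6% |
| 1.5 | 0.0712 → 0.0708 | 94.7% → 94.6% |
| 2.0 | 0.0721 → 0.0700 | 94.4% → 94.9% |
| 3.0 | 0.0712 → 0.0666 | 94.6% → 96.5% |

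A separate run at an odds ratio of 2.5 gave 94.2% → 95.8%. At an illustrative 0.83 v 0.73, which the protocol does not use, power went from 77.3% to 79.4% (odds ratio 2.0) and from 76.7% to 80.6% (2.5).

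Across independent runs and settings, the SE falls by about 1%, 3-4% and 5-8% at odds ratios of 1.5, 2.0 and 2.5. Since 1/0.99² = 1.02, 1/0.97² to 1/0.96² = 1.06 to 1.09, and 1/0.95² to 1/0.92² = 1.11 to 1.18, this is worth about 2%, 6-9% and 11-18% more patients.

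**4. Size of the chance imbalance.** The part of the crude SE due to area is √(0.0721² − 0.0700²) = 1.7 points at odds ratio 2 and √(0.0712² − 0.0666²) = 2.5 points at odds ratio 3, within a total SE of about 7 points.

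**5. Error at the margin** (0.63 v 0.73): 2.2-2.7% adjusted and 2.4-3.1% crude in the runs of step 3. Adjustment for area alone does not inflate it.

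**6. Adding centre.** At the planned rates, 60×0.12 + 60×0.27 = 23.4 non-responders are expected across eight centres, about 3 each if the centres are equal. With eight equal, unpooled centre terms, about 25% of simulated trials at the planned rates had no converged fit, because some centre had no failures. Error at the margin was 2.9-3.5%, against 2.2-3.0% for Newcombe-Wilson in the same trials (Monte Carlo error about 0.3).

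**The case against.** The strongest reply is that nothing here is wrong. Randomisation makes the crude difference unbiased, its interval already covers chance imbalance, and the sample size was computed for the same crude comparison. All of that stands. A reader might infer that the primary result would be biased or its error rate compromised; the document does not support that.

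A reader might also infer that precision is certainly being lost. That is not shown either. The 16 cm² threshold suggests that area was thought relevant, but the document gives no reason for it and no estimate of how area relates to haemostasis. With a weak link the gain is nil or slightly negative.

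A third point is that the statistical analysis plan is not shown and may add an adjusted analysis. It may, as a supportive one. But the protocol itself fixes the crude difference as the primary criterion, so a plan that made an adjusted estimate primary would depart from it.

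Finally, the timing of the paper blot is not stated, and the investigator knows the product once the envelope is opened. The surface is certainly fixed before allocation, but of the two measures of it only the surgeon's estimate is certainly made before allocation. This limits which measure can be used; it does not rule out adjustment.

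**Conclusion.** The point holds as a possible improvement in efficiency, not as an error. The protocol fixes an unadjusted primary difference and does not use a recorded characteristic that treatment cannot alter. Under assumed odds ratios of 1.5 to 2.5 per SD of log area, the SE would fall by about 1% to 8%. Power would rise by about 0-2 points at the planned rates and about 1-4 points at 0.83 v 0.73. If area is not prognostic, the cost is under 1% of the SE. The figures assume a normally distributed log area, a correctly specified logistic model and no centre terms. Importance is low: the planned conclusion is unlikely to turn on this unless the true difference is much smaller than 15 points and area is clearly prognostic.

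**What to change.** Before outcomes are seen, amend Primary Variable to pre-specify:
- **Estimate:** a standardised (g-computation) risk difference from a logistic model with treatment and log resection area, with a robust or influence-function 95% interval tested against -0.100. It stays on the marginal risk-difference scale, so the margin keeps its meaning.
- **Covariate:** the blot area only if the blot is taken before the envelope is opened; otherwise the surgeon's pre-allocation estimate. The protocol should say which.
- **Centre:** no unpooled centre terms in the logistic model. Account for centre only through a pooling rule stated in advance or a stratified variance.
- **Sensitivity analysis and fallback:** the crude Newcombe-Wilson interval, which also becomes the primary result if the model does not converge.

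The cost is protocol wording and a few lines of code. Area is already collected. If the surgeon's estimate is used, it must be recorded as a number and not only as a pass against 16 cm²; the article does not say which is done. The downside is a model-based interval and a negligible loss of precision if area is not prognostic.

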### Sample size

The sample size was calculated to test for non-inferiority of Treatment Arm 1 (Sangustop^®^) versus Treatment Arm 2 (Tachosil^®^) in terms of haemostasis 3 minutes after application of the haemostatic product. The proportion of patients with a complete haemostasis 3 minutes after application will be assessed. In a previous study [4] the proportion of patients with complete blood clotting after 3 minutes for Tachosil^® ^was estimated to be 73%.

With 60 subjects in each group, the lower limit of the observed one-sided 97,5% confidence interval will be expected to exceed -0,100 with 93% power when the proportion of Treatment Arm 2, π_S_, is 0,730 and the expected proportion of Treatment Arm 1, π_T_, is 0,880; results are based on 100 simulations using the Newcombe-Wilson score method to construct the confidence interval [7].

In case of non-inferiority an additional two group χ^2^-test with a 0,050 two-sided significance level will have 83% power to detect the difference between an Treatment Arm 2 proportion, π_1_, of 0,730 and an Treatment Arm 1 proportion, π_2_, of 0,930 (odds ratio of 4,914) when the sample size in each group is 60.

Assuming a drop-out rate of 5% a total number of 126 patients needs to be enrolled. Figure 1 shows a flow diagram of the progress through the trial phases.

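### The 83% superiority power is correct for its stated inputs, but matches neither the planned Fisher test nor the Sangustop rate the article calls expected

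*Protocol article*

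**What the plan says.** The Sample size section of the protocol article makes two power statements. Both use 60 patients per group and a Tachosil 3-minute haemostasis proportion of 0.73.

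- **Non-inferiority.** Power is 93% against a margin of -0.10, with "the expected proportion of Treatment Arm 1" set at 0.88 and a Newcombe-Wilson interval.
- **Superiority.** The paragraph begins "In case of non-inferiority an additional two group χ^2^-test" and goes on: "with a 0,050 two-sided significance level will have 83% power to detect the difference between an Treatment Arm 2 proportion" of 0.73 and a Sangustop proportion, which here is 0.93, with an odds ratio of 4.914. The article does not say how 0.93 relates to 0.88.

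The Primary Variable section gives two routes to superiority. If the 95% interval lies not only above -0.1 "but also above zero then there is evidence of superiority in terms of statistical significance at the 5% level". The next sentence says the difference in proportions "will be tested with a Fisher's exact test to reject the null hypothesis of no difference". The chi-square test of the Sample size section does not appear there, and that section does not name the interval method.

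**The concern.** The power statement and the analysis it is meant to describe differ in two ways.

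1. **Effect size.** Two adjacent paragraphs use different Sangustop rates. Only 0.88 is called expected, yet the superiority power is given at 0.93 alone. A reader who takes the two powers as describing one scenario will think superiority has an 83% chance of being shown if Sangustop performs as expected.
2. **Test.** The power is computed for a chi-square test, while the analysis uses Fisher's exact test, which is more conservative at this sample size.

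What is at stake is how a non-significant superiority result is read. Someone relying on 83% would take it as fair evidence against an advantage for Sangustop. At the expected rate, such a result would be about as likely as not.

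**Working it through.** **Inputs.** From Sample size: 60 per arm; Tachosil 0.73; Sangustop 0.93 (superiority paragraph) or 0.88 (non-inferiority paragraph); two-sided 5% level; chi-square test. From Primary Variable: Fisher's exact test, or a 95% interval above zero. The Newcombe-Wilson method for that interval is an assumption, carried over from the non-inferiority power statement.

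**Step 1: reproduce the stated 83%.** The normal approximation with pooled variance under the null is

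power = Φ{ [d − 1.96·√(2·p̄(1−p̄)/n)] / √([p₁(1−p₁) + p₂(1−p₂)]/n) }

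- d = 0.93 − 0.73 = 0.20 and p̄ = 0.83.
- Null standard error: √(2 × 0.83 × 0.17 / 60) = 0.0686; times 1.96 = 0.1344.
- Alternative standard error: √((0.1971 + 0.0651)/60) = 0.0661.
- (0.20 − 0.1344)/0.0661 = 0.992, so power = 0.839.

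This agrees with 83% to within one percentage point. The odds ratio also reproduces: (0.93/0.07)/(0.73/0.27) = 4.914.

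**Step 2: same formula at the expected rate, 0.88.**

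- d = 0.15 and p̄ = 0.805.
- Null standard error: √(2 × 0.805 × 0.195 / 60) = 0.0723; times 1.96 = 0.1418.
- Alternative standard error: √((0.1971 + 0.1056)/60) = 0.0710.
- (0.15 − 0.1418)/0.0710 = 0.116, so power = 0.546.

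The odds ratio at 0.88 is (0.88/0.12)/(0.73/0.27) = 2.71.

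**Step 3: exact power for each possible rule.** Sum over all outcomes a (Sangustop successes) and b (Tachosil successes):

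power = Σₐ Σ_b Bin(a; 60, p_T) · Bin(b; 60, 0.73) · 1{rule met in favour of Sangustop}

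The rules are Fisher p ≤ 0.05, uncorrected chi-square p ≤ 0.05, and Newcombe-Wilson lower 95% limit above zero.

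| Rule, 60 per arm, Tachosil 0.73 | Sangustop 0.93 | Sangustop 0.88 |
|---|---|---|
| Chi-square (Sample size) | 85.4% | 55.3% |
| Newcombe-Wilson interval above zero (method assumed) | 85.2% | 54.1% |
| Fisher's exact test (Primary Variable) | 79.5% | 45.9% |

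**Step 4: separate the two effects.** Moving from 0.93 to 0.88 with the chi-square test costs 85.4 − 55.3 = 30.1 points. Moving from chi-square to Fisher costs a further 55.3 − 45.9 = 9.4 points at 0.88, or 85.4 − 79.5 = 5.9 points at 0.93. The rate is the main driver.

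**Step 5: the two planned criteria are not interchangeable.** At 0.88 the interval rule has 54.1 − 45.9 = 8.2 points more power than Fisher's test. Under the Newcombe-Wilson assumption, at least about 8% of such trials would therefore meet the interval rule and fail Fisher's test.

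**Step 6: sensitivity to the number analysed.** Fisher power at 0.88 is 43.7% with 57 per arm and 48.6% with 63 per arm (all 126 analysed), so the conclusion does not depend on the drop-out assumption.

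**Step 7: check the primary power.** Exact enumeration of the Newcombe-Wilson lower limit above -0.10 at 0.88 v 0.73 gives 94.1%, consistent with the stated 93%.

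**The case against.** The strongest reply is that nothing is miscalculated. The 83% is right for the test and rates printed beside it, and both 0.93 and the chi-square test are the article's own. That stands: a reader might infer an arithmetic error, and Step 1 shows there is none.

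Second, the superiority sentence speaks of power to detect a difference, and the word expected is attached only to 0.88. So 0.93 can be read as the difference that a sample size fixed for non-inferiority could detect. That reading is fair, and on it the two rates do not contradict each other. But the article does not state it or show how much lower the power is at 0.88. The mismatch of tests remains on either reading.

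Third, if superiority is judged by the interval and the interval is Newcombe-Wilson, power at 0.93 is 85.2%, in line with the stated figure. That also stands, but only for 0.93; at 0.88 it is 54.1%. The article does not say whether the interval or Fisher's test decides.

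Fourth, superiority is an additional step, and the Discussion itself doubts its clinical relevance. This limits the weight of the point. A reader might infer from 46% that the trial is too small, but the sample size was set for non-inferiority and that power reproduces.

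A reader might also infer that the larger rate was chosen to carry the figure past 80%. The article gives no reason for 0.93, so nothing supports a statement about motive.

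**Conclusion.** This is an internal inconsistency that should be corrected; it is not an arithmetic error and not a flaw in the primary design. The stated 83% belongs to a chi-square test at 0.93. With the planned Fisher test, power is 79.5% at that rate and about 46% at the rate the article calls expected. By the interval rule it is about 85% and 54%.

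These figures assume 60 analysed per arm, a true Tachosil rate of 0.73, independent binomial outcomes and, for the interval rule only, the Newcombe-Wilson method. The non-inferiority sample size, margin and conclusion are unaffected.

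**What to change.** 1. Name one decision rule for superiority, either Fisher's exact test or a stated confidence-interval method, and use it in both the Sample size and Primary Variable sections.
2. Label 0.93 as a detectable difference and keep 0.88 as the expected rate.
3. State the power of the chosen rule at both rates: 79.5% and about 46% for Fisher's exact test, or about 85% and 54% for the Newcombe-Wilson interval.

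This is a change of wording and needs no extra patients. The only cost is a less favourable stated power for a step that is additional to the primary objective.
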